## Abstract

**Background:**

Stroke is a major cause of morbidity and mortality, especially in low and middle income countries. Medical management is the mainstay of therapy to prevent recurrence of stroke. Current estimates are that only 1 in 6 patients have perfect adherence to medication schedules. Using SMS (Short Messaging Service) as reminders to take medicines have been used previously for diseases such as diabetes and HIV with moderate success. We aim to explore the effectiveness and acceptability of SMS in increasing adherence to medications in patients with stroke.

**Methods:**

This will be a randomized, controlled, assessor blinded single center superiority trial. Adult participants with access to a cell phone and a history of stroke longer than 1 month on multiple risk modifying medications will be selected from Neurology and Stroke Clinic. They will be randomized into two parallel groups in a 1:1 ratio via block technique with one group receiving the standard of care as per institutional guidelines while the parallel group receiving SMS reminders for each dose of medicine in addition to the standard of care. In addition intervention group will receive messages for lifestyle changes, medication information, risk factors and motivation for medication adherence. These will bemodeled on Social Cognitive Theory and Health Belief Model and will be categorized by Michies Taxonomy of Behavioral Change Communication. Patient compliance to medicines will be measured at baseline and then after 2 months in each group by using the Morisky Medication Adherence Scale. The change in compliance to medication regimen after the intervention and the difference between the two groups will be used to determine the effectiveness of SMS reminders as a tool to increase medication compliance. The acceptability of the SMS will be determined by a tool designed for this study whose attributes are based Rogers Diffusion of innovation theory.

A sample size of 86 participants in each arm will be sufficient to detect a difference of 1 point on the MMAS with a power of 90 % and significance level of 5 % between the two groups; using an attrition rate of 15 %, 200 participants in all will be randomized.

**Discussion:**

The SMS for Stroke Study will provide evidence for feasibility and effectiveness of SMS in improving post stroke medication adherence in an LMIC setting.

**Trial registration:**

https://clinicaltrials.gov/ct2/show/NCT01986023 11 /11/2013

**Electronic supplementary material:**

The online version of this article (doi:10.1186/s12883-015-0413-2) contains supplementary material, which is available to authorized users.

## Background

Stroke is a major cause of death and disability worldwide that affects 16 million persons annually [1]. The burden is especially high in low and middle income countries which account for more than 85 % of all stroke related mortality [2, 3]. Pakistan is no different, with a lifetime stroke prevalence of 19 % and a recurrence risk of 53 % in the first year alone [4–7].

Long term mortality due to stroke is most frequently related to cardiovascular disease (cerebrovascular or heart disease) [8, 9]. Predictors include diabetes mellitus, atrial fibrillation, large artery atherosclerosis and ischemic heart disease [10–14], all of which are modifiable through medical management. Effective therapy for stroke hence comprises of a combination of antiplatelet, anti-lipid and antihypertensive therapy [15]. For medical management to be effective however, compliance to medication schedule is the single most important factor.

Current estimates are that only one sixth of all patients come close to perfect adherence to their medication regimen [16]. The issue is gaining importance due to an increase in the prevalence of chronic diseases and an aging population [17]. Common causes of medication non adherence include complex treatment regimens [18] and patient's lack of belief in the treatment [19]. Practical ways to improve medication adherence are still not well established.

Strategies that have previously shown success include telephone calls, behavior therapy and dissemination of information materials relating to adherence [20–22]. These interventions however are often complex and require abundant resources which make them impractical in resource strapped regions [20]. Using innovation and technology offers alternative solutions that may also be able to address the issue of cost and resources. One such solution is the use of the Short Text Message system (SMS). In the last 10 years, there has been an exponential increase in the use of mobile phones in Pakistan. There are currently more than 132 million active mobile phone connections in the country as compared with a little over 5 million in 2004 [23]. This translates to around 77 % of all Pakistanis [23] having access to a cell phone today and with it, SMS. The rise has been due to extremely affordable costs. An SMS in Pakistan costs around 0.27 cents [24]. Use of SMS is thus a potential tool in aiding patients adhere to medication schedules.

SMS has been used previously in diseases such as asthma, HIV and diabetes with variable success [25–36]. However, to the best of our knowledge, tailored SMS for each patient based on their dosing frequency, have not been studied before. Moreover SMS to promote health, that are informed by Health Theory and coded by Taxonomy for replicability, are new and in line with developing the science of informed replicable mHealth interventions [37].

We hypothesize that sending SMS as medication reminders for each dose and promoting healthy behavior will improve medication adherence among stroke patients This trial therefore aims to assess this effect of SMS on patient compliance to medication, by customizing the SMS frequency for each individual according to his/her dosing frequency. The secondary objective is to assess the acceptability and patient satisfaction associated with this intervention. The trial will also attempt establish if an intervention like this is cost effective in a low and middle income setting.

## Methods

### Design overview (Fig. 1 (Study flow chart))

The SMS4stroke trial will be a randomized, controlled, assessor blinded single center superiority trial. The participants will be randomized into two parallel groups in a 1:1 ratio via block technique with one group receiving the standard of care as per institutional guidelines while the parallel group receiving SMS reminders for each dose of medicine in addition to the standard of care. The intervention group will also receive twice weekly SMS that reinforce healthy behaviors and the importance of taking medications.

**Fig. 1 Fig1:**
[figure not shown]
Study Flow Chart

**Fig. 2 Fig2:**
[figure not shown]
Screenshots of SMS (Templates)

### Study setting

The trial will be conducted in the Neurology & Stroke Clinic at the Aga Khan University Hospital (AKUH), Karachi, Pakistan. The center is a Joint Commission International Accreditation (JCIA) accredited tertiary care hospital located in Karachi, a large metropolitan city located in the south of Pakistan. Stroke service is delivered through a 24 h emergency neurovascular team and ambulatory care clinics. The hospital caters to a large and diverse population with an estimated 100 patients attending Neurology & Stroke Clinic each day. The average annual stroke clinic volume is 1500 patient visits. The center also has logistic and technical expertise available from dedicated research support staff and an independent Clinical Trials Unit (CTU) and a dedicated Aga Khan Development Network e-Health Resource Center.

### Participants

Participants will be selected from patients who present to the Neurology and Stroke Clinic at the center.

#### Inclusion criteria

Age greater than 18 years oldHistory of stroke(s) confirmed by neuroimaging at the time of the episode>1 month since last episode of strokeUse of at least two drugs such as (but not limited to) anti platelets, statins, anti-hypertensives to control risk factors of stroke.Modified Rankin Score of 3 or less.Possession of a personal cell phone that the patient has access to at all times. In the case of patients who do not own or are unable to use mobile phones, they must have a caregiver available at all times who possesses a cell phone.Ability to receive, comprehend and reply to an SMS in English, Urdu or Roman Urdu. In the case of patients who themselves are unable to receive, comprehend or reply to an SMS, they must have caregivers available at all times who could perform the above mentioned tasks.

In addition all participants will be required to provide a written, informed consent prior to enrollment Additional file 1.

#### Exclusion criteria

Biological impairment in reading or responding to SMS such as (but not limited to) loss of vision, visual field cuts, aphasia.Diagnosed organ dysfunction or malignancy such as liver failure, renal dysfunction etc. that require frequent medication changes.Plans to travel outside the country inside the two months following enrollment and during SMS intervention with a SIM unable to receive text messages.

### Interventions

#### Control group

In the control group, patients will receive the usual standard of care provided at the center for stroke patients. This primarily consists of regular follow up visits (frequency as per patient needs) with their stroke neurologist. The standard schedule for clinic visits after an uncomplicated recovery is 2 weeks, 1 month, 3 months and 6 months after index stroke. On each clinic visit, a detailed neurological examination is performed, stroke risk factors are assessed and concerns and queries are addressed. In addition, the patient is counseled regarding beneficial life style modifications and the significance of compliance with medication regimens. Reading material about their disease in English or Urdu is offered to each patient. None of these activities however are extended beyond their clinic visit. Each patient is, however, provided with a telephone number that can be used to reach the stroke team in case of an emergency and each patient is also reminded of their clinic appointments 1–2 days prior via SMS and/or phone as per center policy.

#### Intervention group

In addition to the standard of care as provided to the control group, automated SMS serving as reminders for patients to take their medicines will be sent to each patient in the intervention group. These SMS will be sent at the time patients are scheduled to take their medications, i.e. once, twice or thrice daily as advised by their physician. The text will be sent for each dose once, collectively for all drug groups; hence some patients might receive multiple SMS in a day. The participants will be required to respond to the SMS stating whether or not they have taken their medicines for that time. The patient response will be recorded. No action will be taken if the patient does not reply to an SMS or if the patient responds saying that they have not taken the medicine. The patient will be reached via phone call if he/she fails to respond for at least 5 consecutive days to identify the reason.

Furthermore, SMS will be sent twice weekly to each patient in the intervention group that reinforces the importance of taking medications and other healthy behaviors. These SMS will be customized to each patient’s risk profile and medications by the research team. For example, some of these SMS will be drug specific i.e. they explain the benefit of a particular drug and so they will only be sent to those taking that drug. The SMS will be phrased using Michie et al’s taxonomy for behavior change interventions [38]. The health information messages will cover information about disease, modifiable risk factors, drug information and importance of optimal drug adherence. These are 16 different messages, tailored to individual patients and will be sent over an 8 week period twice weekly. The set of messages for each patient will be selected at the time of recruitment and then sent at the scheduled timings by our IT staff. These messages will change during the duration of the study for the participant based on their profile for e.g. a non-smoking participant is not to get a message about quitting smoking. However for the overall study these are standardized messages that have been worded and coded carefully.

Using the standardized definitions as presented in the taxonomy allows for easy reproducibility and generalized applicability for future work related to this intervention. The specific content of the SMS is derived based on the Social Cognitive theory [39] and Health Belief model [40] of behavior change in health care. Templates used include “Stroke can happen again. Don’t forget to take your medicine” and “High blood pressure can cause stroke. Please take your blood pressure medicine.” The purpose of adapting this model for designing SMS is to make them effective in communicating to the participants the consequences of their behavior on health (Fig. 2).

Additional file 2 provides details of these SMS along with the taxonomy number for each SMS design. The definitions of each taxonomy are also provided in the appendix.

The Frontline SMS software will be used to send the SMS. The software has open access and is free to use. Additional file 3 describes the software usage for this specific study.

### Outcomes

The primary outcome of interest will be a change in medication adherence after 2 months of receiving the SMS. These findings will be compared to its corresponding findings from the control group to account for the Hawthorne effect.

Medication adherence will be measured at recruitment and after 2 months in both groups on the Morisky Medication Adherence Scale [18]. The scale has been used in a similar setting previously and it has been translated and validated in Urdu [41]. The change will be determined by comparing the score on the MMAS before and after the intervention.

The instrument consists of 8 questions and the response to each question is scored as either 0 or 1. The maximum score, hence, through this questionnaire is 8. A higher score indicates better adherence. A score of < 2 indicates low adherence.

Secondary outcome measures include patient satisfaction and acceptability of using an e-health based innovation such as the SMS to improve clinical outcome. This will be done through a tool that has been designed for IT based interventions and adapted for this study. This tool identifies beneficial and untoward attributes of the SMS for stroke intervention by users. The tool design for measuring acceptability of innovation is based on Roger's Diffusion of Innovations theory. The tool hence has questions that specifically assess the relative advantage of SMS, its compatibility with the study population, its complexity, its trialability and observability [42].

### Participant timeline

Recruitment will begin with signing of an informed consent and assigning the patient an ID number. Data collection will begin with a detailed interview regarding the demographic and clinical details of the patient including his/her prescription details. The baseline MMAS score for each patient will also be calculated at this time. This will be followed by the research staff leaving the room and a senior investigator (QS) taking over at which point the patient will be randomized to either the intervention or the control group by the independent CTU staff.

If the patient is allocated to the intervention arm, the investigator (unblended) will explain the details of the intervention and will demonstrate by sending one test SMS on his/her cell phone (in English and Urdu both).

If there is a change in patient prescription with respect to any drug or dose by any physician, the patient will be requested to notify at a 24 hours helpline number answered by trained staff. In addition, since participants are tagged in the hospital system as trial participants all visits are logged and there will be tracking to ascertain any changes in prescription which will be medically confirmed.

Following the recruitment visit, the patients will not be required to come back to clinic for any additional visits for the purposes of this study for 2 months at which time there will be a follow up interview. At this time, patient adherence will be assessed by the research officer again who will be blinded.

### Duration

The trial will continue till achievement of sample size and 2 months follow up for outcome ascertainment thereafter.

### Sample size

Based on literature, we estimated the mean MMAS score to be 6 [43] in the control arm and 7 in the intervention group, giving a mean difference of 1. A standard deviation of 2 is assumed for this score. Using these values, a sample of at least 172 subjects will be required to achieve a power of 90 % and significance level of 5 % when testing a two tailed hypothesis. This translates into 16 % effect size as hypothesized. Keeping a 15 % attrition rate the sample size was inflated so that at least 100 subjects will be targeted for each arm in the sample.

### Assignment of interventions

Cards with patient assignments to either the intervention or the control group will be prepared by the CTU through computerized block randomization technique in block sizes of 10. This is to ensure similarity between the two groups at all times permitting interim analysis during the study. Additionally block size was not discussed with the research team interacting with participant recruitment to limit predictability of assignment and researcher bias.

The randomization cards will be sealed in opaque envelopes, marked by ID and kept with the CTU. Even if the envelope is held against bright sunlight one will not be able to ascertain the allocation. After enrollment, obtaining informed consent and completing the baseline measurements, the CTU will be informed and randomization of the participant will be done.

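### One fixed block size of 10, withheld from recruiters but printed in the article, would make about 1 in 6 assignments certain to anyone who learns it and tracks allocations

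*Protocol article*

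**What the plan says.** The Design overview describes a "randomized, controlled, assessor blinded single center superiority trial" with participants "randomized into two parallel groups in a 1:1 ratio via block technique". Assignment of interventions gives the method as "computerized block randomization technique in block sizes of 10"; it names no other size and no stratification. The stated reason for blocking is to keep the groups similar throughout, so that an interim analysis is possible.

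The same section recognises the risk of prediction: "Additionally block size was not discussed with the research team interacting with participant recruitment to limit predictability of assignment and researcher bias". It adds sealed opaque envelopes kept by the CTU, and says the CTU is told of a participant only after enrolment, consent and baseline measurement.

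Under Participant timeline, research staff do the interview and baseline adherence score and leave the room. A senior investigator takes over, and "the patient will be randomized to either the intervention or the control group by the independent CTU staff". Then: "If the patient is allocated to the intervention arm, the investigator (unblended) will explain the details of the intervention" (the bracketed word is evidently a misprint for unblinded). Sample size says "at least 100 subjects will be targeted for each arm in the sample". Trial status is given only as ongoing.

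**The concern.** A constant block length protects an open single-site trial only while nobody who handles enrolment both knows the length and can count allocations. Here one person is placed to count: the investigator who takes over at each randomisation and learns the result. The other half of the protection, secrecy of the length, is given up by the article. Opaque envelopes stop a card being read early. They do not stop the next card being deduced from those already opened.

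At stake is selection before randomisation. If someone able to foresee the next arm could influence who is enrolled next, or when, motivated or well-supported patients could gather in one arm. The primary outcome is self-reported adherence, which the article's Discussion names as its major limitation, so such factors plausibly affect it. Neither assessor blinding nor intention-to-treat analysis corrects this kind of selection.

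**Working it through.** **Inputs.** Block size 10 (Assignment of interventions); 1:1 ratio, so 5 + 5 per block, and one centre (Design overview); 100 per arm, so 200 randomised (Sample size), which makes 20 blocks. Assumption: one unstratified list, because no stratification is described.

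**The plan's own figures.** The article states no predictability figure. The sample size only turns a share into a count. It reproduces: for a difference of 1, SD 2, two-sided 5 % and 90 % power, the exact t-test needs 86 per arm (power 0.8999 at 85, 0.9032 at 86), hence 172.

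**Certain assignments, fixed block of 10.** An assignment is certain once one arm has used its 5 places. There are C(10,5) = 252 equally likely sequences. The chance that exactly the last *d* assignments are certain is 2·C(9−d, 4)/252:

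| d | 1 | 2 | 3 | 4 | 5 |
|---|---|---|---|---|---|
| share of blocks | 0.556 | 0.278 | 0.119 | 0.040 | 0.008 |

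The mean is 1.667 per block. The closed form for a block of 2m agrees: 2m/(m+1) = 10/6 = 1.667, a share of 1/(m+1) = 1/6 = 16.7 %. Over 20 blocks this is 20 × 1.667 = 33.3 of 200. The last assignment of every block is always certain, and the last two or more are certain in 1 − 0.556 = 44 % of blocks.

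**Best guess.** Always guessing the arm that is behind gives m + (4^m / C(2m,m) − 1)/2 correct guesses per block. For m = 5: 5 + (1024/252 − 1)/2 = 6.53 of 10, or 65.3 % (about 131 of 200), against 50 % by chance. This strategy needs only a tally of past allocations. Certainty needs the block size as well.

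**Alternatives.** For randomly mixed sizes, sequences of 200 were simulated. The observer is assumed to know the set of sizes but not their order. Best-guess accuracy can also be checked by hand from the correct guesses per block: 2.833 for size 4, 4.100 for 6, 5.329 for 8, 6.532 for 10 and 7.716 for 12.

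| Scheme | Certain | Best guess correct | Largest imbalance |
|---|---|---|---|
| fixed 10 | 16.7 % | 65.3 % | 5 |
| random 4/6/8 | about 2 % | (2.833+4.100+5.329)/18 = 68.1 % | 4 |
| random 8/10/12 | about 1 % | (5.329+6.532+7.716)/30 = 65.3 % | 6 |

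Both mixes remove nearly all certainty. The small-block mix does so at the price of easier guessing; the mix centred on 10 does not.

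**The case against.** Three stronger readings are tempting, and the article does not support them.

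- A reader might infer that the block size was published during recruitment. The status says only ongoing. The Duration section runs the trial until the sample is reached plus 2 months of follow-up, and the ethics section expects a trial of around 3 months. The status therefore also fits a trial that had closed to recruitment, in which case publication did no harm. Equally, nothing says that recruitment had closed.
- A reader might take 1 in 6 as the share of assignments that is in fact predictable. It applies only to someone who knows the size and has the complete ordered list. The size was deliberately kept from the recruiting team. That a constant length could be worked out from the running sequence is possible, but nothing here quantifies it.
- A reader might infer that patients could be steered before consent. The documented order is against that: other staff take consent and baseline, independent CTU staff randomise, and the investigator who learns the allocation comes in afterwards. No section gives that investigator a role in screening or in the timing of enrolment. None excludes one either, so steering is possible but not shown.

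It is also fair to say that 10 resists guessing better than smaller blocks do, so replacing it with small varying blocks would be a trade-off and not a plain gain.

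What stands: one fixed size, reliance on its secrecy, its disclosure in the article, and an unblinded person able to keep the tally.

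**Conclusion.** The point holds as a conditional weakness of modest weight. For an observer with the block size and the allocation list, 16.7 % of assignments (about 33 of 200) are certain. This rests on a single unstratified list with every block of length 10. Whether anyone was in that position while enrolment continued cannot be settled from the article, and there is no evidence that selection occurred. The authors saw the risk and reduced it in part. The safeguard they singled out against prediction is the one that publication weakens, provided recruitment was still open.

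**What to change.** **If recruitment is open:** the CTU generates the remaining sequence with randomly varying block sizes that are not all smaller than 10, for example 8, 10 and 12. The CTU alone holds the sizes and discloses them after recruitment closes. The change is best made at the end of a current block, so that no partial block adds to the imbalance. The article should also state whether the senior investigator has any part in screening or in the timing of enrolment.

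**Cost:** regenerating the unused envelopes, with no effect on participants already randomised. The largest imbalance rises from 5 to 6. At the planned interim look, 25 % of 200 = 50 participants, the worst split would be 28 to 22. Relative efficiency against an even split is then 4 × 28 × 22 / 50² = 0.986, so the stated purpose of blocking is still met.

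**If recruitment has closed:** say so, and report the single fixed block size, with the conditional 1-in-6 figure, as a limitation.
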